## Abstract

**Background::**

Episodes of malnutrition in early childhood can produces alterations in the salivary glands. The investigation of mechanisms that can reduce the impact of malnutrition on the defenses of the organism is of the utmost important and interest to public health. The aim of this study is to evaluate the effect of low-level laser on the saliva of children aged 1 to 5 years with energy-protein malnutrition.

**Methods::**

Mandatory inclusion criteria are diagnosis of malnutrition. The sample will consist of 50 men and women malnourished children aged 12 to 71 months. Saliva will be collected and the volume of saliva will be measured and the salivary flow rate will be determined (mL/min). Concentrations of salivary IgA in all samples will be measured using a commercial Enzyme-Linked Immunosorbent Assay (ELISA) kit. Low-level laser (laser diode) will be administered in the region of the parotid glands bilaterally as well as in the regions of the submandibular and sublingual glands.

**Discussion::**

This study will be the first that investigate the effects of local laser therapy on the salivary glands of malnourished children.

**Trial registration::**

Clinical.trials.gov as NCT03355313, first received in 21 November 2017.

## Background

1

Malnutrition is a clinical–social disease caused by multiple prenatal, intrauterine, and postnatal factors as well as social, political, and cultural determinants (distal causes).^[1]^ Despite the global and national reductions^[2]^ in the number of cases, malnutrition continues to be a public health problem, with greater prevalence in pockets of poverty found in the northern and northeastern regions of Brazil.^[3–6]^

Energy-protein malnutrition occurs when there is an imbalance between food intake and the physiological expenditure of energy and nutrients in all cells of the body, including those responsible for the formation of dental tissue, saliva, and the oral epithelium.^[7]^ Thus, malnutrition means that cells do not receive the nutrients necessary to perform their functions of energy production, tissue formation/repair, and the regulation of their own functioning.^[8,9]^

Malnutrition in the early years of life leads to growth deficits in childhood, as reflected by anthropometric indicators. This condition is also associated with a higher child mortality rate, greater probability of acquiring infectious diseases, impaired psychomotor development, and poorer academic performance as well as lower productivity in adulthood.^[10,11]^

Episodes of malnutrition in early childhood, with consequent calcium, phosphate, and vitamin A, C and D deficiencies, can increase one's susceptibility to dental caries through 3 probable mechanisms: defects in tooth formation (odontogenesis), delayed tooth eruption, and alterations in the salivary glands.^[12,13]^

It is likely that the significant increase in susceptibility to caries in malnourished individuals stems from alterations in the salivary secretion rate, since a reduction in salivary flow (salivary gland atrophy) increases the susceptibility to both dental caries and dental erosion.^[14–16]^ As saliva is the main defense factor of the oral cavity, a reduction/change in its physical properties (secretion rate and buffering capacity) can cause immunological disorders that affect an individual's defense capacity.^[17]^

Studies have demonstrated that salivary Immunoglobulin A (IgA) also plays an important role in the immunity of the oral mucosa.^[18–20]^ Indeed, patients with IgA deficiency can experience recurring upper airway (tonsillitis, ear infection, and sinusitis), lower airway (pneumonia), and gastrointestinal (diarrhea and parasitosis) infections.^[21]^

IgA was first identified in 1959 by Heremans^[22]^ and is found in serum and organic fluids, such as saliva. There are 2 types of this antibody. IgA1 is produced by B cells of the bone marrow and IgA2 is produced by B cells of the mucosa, accounting for approximately 80% of the total production. Once produced by plasmocytes (differentiated from activated B cells) in the lamina propria of the epithelium of the salivary glands, IgA binds to a polymeric Ig receptor in the base of the epithelial cells, where it is transported and released through proteolytic cleavage to join other substances that compose the salivary mucus.^[21,23]^

Stimulated and non-stimulated salivary flow rates can be reduced significantly in individuals who have suffered severe malnutrition in early childhood as well as those with continued nutritional stress. Thus, malnutrition can exert a continual effect on the reduction in salivary gland function in adolescence as result of malnutrition in early childhood, which suggests that exocrine systems can be compromised for long periods after exposure to malnutrition.^[24]^

The investigation of mechanisms that can reduce the impact of malnutrition on the defenses of the organism is of the utmost important and interest to public health. Among such mechanisms, low-level laser therapy has demonstrated effectiveness in the treatment of diverse conditions and disease through the promotion of the biomodulation of the cell metabolism and due to its analgesic and anti-inflammatory properties with no mutagenic or photothermal effects.^[25]^ The conversion of laser light into useful energy for cells through photochemical and photophysical reactions can simulate the production of mitochondrial adenosine triphosphate (ATP), cell proliferation, and protein synthesis.^[26,27]^

Laser stimulation of the major salivary glands to produce more saliva occurs through the increase in local circulation due to vasodilatation, the induction of the proliferation of glandular cells and cell respiration/ATP synthesis as well as the release of growth factors and cytokines to stimulate protein exocytosis.^[25]^ Regarding an increase in salivary IgA, low-level laser intensifies the activation of B lymphocytes, which differentiate into plasma cells, thereby contributing to the increase in immunoglobulin levels.^[28]^

It is important to study the impact of malnutrition in children because its long-term consequences could be reduced which implies promoting positive effects on oral and general healthy.

The primary aim of this trial is to evaluate the effect of low-level laser on the saliva of children aged 1 to 5 years with energy-protein malnutrition. Secondary outcomes are to establish the degree of malnutrition in children aged 1 to 5 years and to analyze the saliva of children aged 1 to 5 years with energy-protein malnutrition.

## Methods/Design

2

### Type of study

2.1

An experimental cross-sectional study is proposed, which will be conducted at the Center for Educational and Nutrition Recovery (CREN) in the city of Maceió, state of Alagoas, Brazil.

### Trial registration

2.2

Clinical.trials.gov as NCT03355313, first received in 21 November 2017, https://clinicaltrials.gov/ct2/show/NCT03355313.

### Sample

2.3

#### Characteristics and size

2.3.1

This cross-sectional study will use a sample of children aged 12 to 71 months of the 7th Administrative Region of Maceió. This region is one of the poorest region in Maceió. The children's parents/guardians will be interviewed at the CREN in the city of Maceió, state of Alagoas, Brazil. The sample size was estimated considering a prevalence of malnutrition of about 10% in children under 6 years old, with statistical power of 80% and 95% significance, resulting in a sample of 50 children.

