### Administration of low level laser

2.9

Low-level laser will be administered using the Photon Lase III device (DMC Equipamentos LTDA, São Paulo, Brazil). Laser will be administered for 10 seconds on 4 intraoral points and 4 extraoral points in the region of the parotid glands bilaterally as well as 1 intraoral point and 1 extraoral point in the regions of the submandibular and sublingual glands. The first session will occur after the collection of saliva. The second and third sessions will be performed 7 and 14 days after the first session, respectively. The final saliva collection will be performed after the third laser session.^[34,35]^

The laser will be adjusted according to the following parameters: Central wavelength (nm) = 808; spectral band width (FWHM) (nm) = 2; operational mode = continuous; mean radiant power (mW) = 100; polarization = randomized; aperture diameter (cm) = 0.2; irradiation at aperture (mW/cm^2^) = 2500; beam profile = multimodal; beam spot on target (cm^2^) = 0.04; irradiation at target (mW/cm^2^) = 2500; exposure time (s) = 40; Radiant exposure (J/cm^2^) = 100.0; radiant energy (J) = 4; number of points irradiated = 10; irradiated area (cm^2^) = 0.40; application method = Contact; number of treatment sessions = 3; frequency of treatment sessions per week = 1; Total radiant energy (J) = 40.

The salivary flow rate and salivary IgA will be compared before and after of each laser application (after 7 and 14 days) and correlation with the malnutrition will be established. The results will be analyzed using ANOVA and Tukey's contrast test. The level of significance will be 5%.

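### The sample of 50 and its 80% power rest on a malnutrition prevalence, so the stated power does not apply to the primary question, the change in saliva after laser

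*Protocol article*

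**What the plan says.** Section 2.3.1 (Characteristics and size) gives the whole justification in one sentence: "The sample size was estimated considering a prevalence of malnutrition of about 10% in children under 6 years old, with statistical power of 80" per cent. The same sentence adds a significance level written as 95% and arrives at 50 children. It names no endpoint, expected change, SD, margin of error, alternative prevalence, test or sidedness.

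The aims at the end of the Background read: "The primary aim of this trial is to evaluate the effect of low-level laser on the saliva of children aged 1 to 5 years". The children meant are malnourished ones. Establishing the degree of malnutrition is listed among the secondary outcomes. Section 2.9 compares salivary flow and salivary IgA before and after laser application by ANOVA with Tukey contrasts at the 5% level, and adds a correlation with malnutrition.

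The article describes the 50 children in two ways. The Abstract makes a diagnosis of malnutrition mandatory and says: "The sample will consist of 50 men and women malnourished children aged 12 to 71 months". Section 2.5 (Inclusion criteria) asks only for age, enrolment at the centre and consent. Section 2.7.1 then grades the children on a scale that includes an ideal range.

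**The concern.** A power figure belongs to a particular test of a particular effect. Here the only quantity behind it is how common malnutrition is, while the primary question is how much saliva changes within a child. A reader who sees 80% power will take it to describe the laser comparison, and it does not.

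Two further points follow. First, a prevalence and a confidence level alone do not lead to a number of children, so the 50 cannot be checked from what is stated. Second, a prevalence of about 10% has no role in a group in which every child is malnourished, as the Abstract describes it. It could matter only if the 50 are unselected, as the inclusion criteria allow.

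At stake is what the trial says it can detect. If the laser result is null, the published 80% cannot be used to argue that a relevant effect would probably have been found.

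**Working it through.** **Inputs from the article.** Prevalence p = 0.10, power 80% and N = 50 (section 2.3.1). The significance of 95% stated there is read as alpha = 0.05, which agrees with the 5% level in sections 2.8 and 2.9. Sidedness is not stated. No SD or effect on saliva is given anywhere, so effects below are in SDs of the within-child change.

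**1. Can 50 be reproduced from the stated inputs?**

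- *Precision of one proportion:* n = 1.96² × 0.10 × 0.90 / d², where d is the margin. With d = 0.05, n = 138.3, so 139. With d = 0.10, n = 34.6, so 35. Solving for n = 50 gives d = 1.96 × √(0.09/50) = 0.083. Power does not enter this formula, and no margin is stated.
- *One-sample test of p0 = 0.10 against p1, 80% power:* n = [z_α√(0.10 × 0.90) + 0.842√(p1(1 − p1))]² / (p1 − 0.10)². For p1 = 0.20, n = 86 two-sided or 69 one-sided. For p1 = 0.25, n = 41 or 33. A value near 50 needs p1 of about 0.22 one-sided, or between 0.23 (53) and 0.24 (46) two-sided. No alternative is stated.
- *Two proportions, two-sided, total N:* 10% against 20% needs 398. A total of 50 needs 10% against about 45%. No second group is described.

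Each route reaches 50 only with one more input that the article does not give. The stated inputs therefore do not determine 50, but they do not rule it out.

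**2. Does the prevalence fit the sample?** If all 50 are malnourished, prevalence in the sample is 100% by construction and cannot be estimated or tested. If 50 unselected children came from a population with 10% prevalence, about 50 × 0.10 = 5 would be malnourished, and finding 50 malnourished children would take about 50/0.10 = 500.

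**3. What can 50 children detect for the laser question?** The calculation is a two-sided paired t-test, with power from the noncentral t distribution with n − 1 degrees of freedom and noncentrality δ√n, where δ is the mean change divided by the SD of the change scores.

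| Change (SD of change) | Power, 50 pairs, alpha 0.05 |
|---|---|
| 0.2 | 28% |
| 0.3 | 55% |
| 0.4 | 79% |
| 0.5 | 93% |

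| Setting | Detectable change at 80% power |
|---|---|
| 50 pairs, one test, alpha 0.05 | 0.404 SD |
| 50 pairs, alpha 0.025 (flow and IgA) | 0.448 SD |
| 50 pairs, alpha 0.05/3 (rough stand-in for three Tukey contrasts) | about 0.47 SD |
| 45 pairs, one test, alpha 0.05 | about 0.43 SD |

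**4. Correlation with malnutrition** (Fisher's z, n = 50): |r| = tanh[(1.96 + 0.842)/√47] = 0.387.

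**5. If a prevalence is estimated in 50 unselected children:** the margin is ±8.3 points at 10%. Observing 5 of 50 gives a 95% Wilson interval of 4.3% to 21.4%.

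**The case against.** The best defence is that the article condenses a fuller protocol. The missing margin or alternative prevalence may stand there, and with a margin of about 8.3 points or an alternative in the low twenties per cent, 50 comes out. That stands against any charge of miscalculation. It does not rescue the power claim: the article does state a basis, and no omitted detail could turn a prevalence into the parameter for a within-child change in saliva.

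It can also be said that the prevalence serves the secondary aim on the degree of malnutrition. Under section 2.5, read alone, that is possible. The calculation would then support a secondary aim and leave the primary one without any. The children attend a nutrition recovery centre, but the article does not say that enrolment there requires malnutrition.

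A reader might infer more than the document supports:

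- *That 50 is too few.* This does not follow. A change of 0.5 SD would be detected with 93% power in a single paired test; the article gives no expected change to compare with this.
- *That 50 is an arithmetic error, for instance because a 5-point margin needs 139.* The 5-point margin appears nowhere in the article.
- *That a prevalence calculation cannot have power.* A one-sample test of a proportion does have power, and the article does not say whether it planned a test or an estimate.
- *That 10% conflicts with the grading in section 2.7.1, where mild malnutrition starts at −1 SD.* Section 2.3.1 does not say which grade or index its 10% refers to, so no conflict is shown.
- *That a null result would be uninterpretable.* It could still be read from its confidence interval; only the appeal to 80% power fails.

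**Conclusion.** The point holds as a mismatch between the basis of the sample size and the primary aim. The 80% power is tied to a prevalence of about 10% and does not apply to the before/after comparison of salivary flow and IgA. The stated inputs do not determine 50. The prevalence does not fit the 50 malnourished children of the Abstract, and the Abstract and section 2.5 disagree on whether malnutrition is required at all.

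In size, what 50 children offer for the laser question is 80% power at about 0.40 to 0.47 SD of the change scores, depending on how many outcomes and contrasts share the 5%. Below that, power falls to 55% at 0.3 SD and 28% at 0.2 SD. These figures assume 50 complete pairs, a two-sided paired comparison and roughly normal change scores. The alpha/3 figure is an approximation that assumes three time points, and it is not an exact Tukey calculation. Whether a change of this size matters clinically cannot be judged from the article.

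**What to change.** Keep 50 and rewrite the justification in section 2.3.1:

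1. Remove the prevalence as the basis for the laser question, and replace the significance of 95% with the two-sided 5% level if that is what is meant.
2. Name the primary outcome and the contrast, and state the detectable effect with its assumptions. A possible wording, to be adapted: with 50 children giving saliva both before and after laser, a two-sided paired comparison has 80% power to detect a mean change of about 0.40 SD of the change scores for a single test at 5%; about 0.45 SD if alpha is halved for flow and IgA; or about 0.47 SD allowing roughly for three Tukey contrasts. Keep only the version that matches the planned analysis.
3. Allow for incomplete pairs. With 45 pairs, the single-test figure is about 0.43 SD.
4. For the correlation with malnutrition, state that |r| of about 0.39 is detectable with 80% power.
5. Reconcile the Abstract with section 2.5 on whether the 50 must be malnourished. If a prevalence is also to be estimated in unselected children, state its precision separately (about ±8 points at 10%).

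The cost is one paragraph and an aligned eligibility statement, with no extra children, visits or assays. The sponsor exchanges a general claim of 80% power for a specific detectable effect that readers can check.

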### Allocation mechanism

2.4

The allocation sequence will be generated by CREN. The number/symbol of each child will be sent by the computer by the registration model in CREN which is based on the distribution by learning classes. Assessments regarding saliva and nutritional status will be blinding for trial participants and data analysts.

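### The primary aim is causal, but the only planned test of laser is an uncontrolled before/after comparison, so the aim needs restating

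*Protocol article*

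**What the plan says.** All references are to the protocol article.

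- **Aim (Background, last paragraph).** "The primary aim of this trial is to evaluate the effect of low-level laser on the saliva of children aged 1 to 5 years". This is a causal question.
- **Design label (2.1 Type of study).** "An experimental cross-sectional study is proposed". Section 2.3.1 repeats the cross-sectional label.
- **Allocation (2.4 Allocation mechanism).** "The allocation sequence will be generated by CREN", and each child's number or symbol comes from the centre's registration model, "which is based on the distribution by learning classes". The section does not say what children are allocated to.
- **Blinding (2.4).** "Assessments regarding saliva and nutritional status will be blinding for trial participants and data analysts".
- **Intervention (2.9 Administration of low level laser).** "Low-level laser will be administered using the Photon Lase III device". One schedule of three sessions, at 0, 7 and 14 days, is given without restriction to a group. "The first session will occur after the collection of saliva", and the last sample is taken after the third session.
- **Planned comparison (2.9).** "The salivary flow rate and salivary IgA will be compared before and after of each laser application (after 7 and 14 days"), using ANOVA and Tukey's contrast at the 5% level, together with a correlation with malnutrition.

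**The concern.** The aim asks whether laser changes saliva. The analysis asks whether saliva changed between samples taken before and after laser. The two questions coincide only if nothing else could move flow or IgA over the same two weeks or so, and the plan has no concurrent comparison with which to check that.

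The setting supplies one candidate. The children are enrolled at a centre for educational and nutrition recovery, and the Background links malnutrition to reduced salivary flow. Some recovery during the study is therefore possible, though the article gives nothing from which to size it. Regression to the mean is another general possibility.

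At stake is the main conclusion. A significant before/after result would be read as benefit from laser, and no later analysis of the same data could separate the two. The allocation sentence and the cross-sectional label add to the difficulty: the first suggests a comparison that appears nowhere else, and the second does not fit children measured repeatedly around an intervention.

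**Working it through.** **1. Passages side by side.**

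| Element | What the article fixes | Consistent with a causal aim? |
|---|---|---|
| Aim (Background) | Effect of laser on saliva | It is the causal aim |
| Groups (2.1, 2.3–2.6, 2.9) | One sample of 50, one laser schedule, no comparator named | No |
| Allocation (2.4) | A sequence tied to learning classes, not described as random, with no arms | No |
| Test (2.9) | Before versus after laser, no between-group term | No |

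The conclusion follows from this table. The figures below only illustrate its size.

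**2. Inputs.** n = 50 (2.3.1) and a 5% level (2.9), taken here as two-sided because sidedness is not stated. The article gives no expected effect, SD or drift for flow or IgA, and its sample size rests on a malnutrition prevalence of about 10%. There is thus no planned figure for the laser comparison to reproduce. Drift δ is an assumption, in units of the SD of within-child change. The true laser effect is set to zero.

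**3. Paired t-test, baseline versus final sample.** The statistic follows a noncentral t with 49 df and noncentrality δ√50. The critical value for an increase is t(0.975; 49) = 2.010.

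**4. Tukey contrast, closer to the stated analysis.** Assume three time points (baseline, day 7, day 14), the same SD of change for each pair, and error df = (50 − 1)(3 − 1) = 98. The studentized-range critical value is 3.366, so the equivalent t is 3.366/√2 = 2.380. The noncentrality for the baseline to day 14 contrast is again δ√50.

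| Assumed δ | δ√50 | P(significant increase), paired t | P(significant increase), Tukey |
|---|---|---|---|
| 0 | 0 | 2.5% | 1.0% |
| 0.2 | 1.414 | 28.3% | 17.2% |
| 0.3 | 2.121 | 54.8% | 40.2% |
| 0.4 | 2.828 | 79.2% | 67.3% |

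**5. Price of a concurrent comparison in the same 50 children** (80% power, two-sided 5%, in SD of change):

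- Uncontrolled change, n = 50: solve P(T > 2.010) = 0.80 with 49 df and noncentrality d√50, giving d = 0.404. Normal approximation: (1.960 + 0.842)/√50 = 0.396.
- 25 versus 25: solve P(T > 2.011) = 0.80 with 48 df and noncentrality d√(25/2), giving d = 0.809. Normal approximation: (1.960 + 0.842)√(2/25) = 0.792.

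The detectable difference roughly doubles before any gain from baseline adjustment.

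**The case against.** A single-arm before/after study is a legitimate exploratory choice, and the Abstract presents this as the first study of its kind. Nothing obliges the sponsor to add a control. This stands: the required change is to the aim, not to the design.

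A reader might also infer more than the text supports:

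- **That the protocol states every child is treated.** It does not. This is inferred from one unrestricted schedule, no named comparator and a before/after analysis. Figure 1, the schedule of enrolment and assessments, is not visible and could not be checked. Nothing in the visible text contradicts the inference.
- **That children are assigned to groups by class, and so differ in age.** The allocation section reads at least as naturally as the issue of identifiers. That class follows age is not stated, and no between-group laser contrast is planned that such an imbalance could bias.
- **That children improve at the collection task with repetition, or recover measurably in 14 days.** The article shows neither. The Background says that gland function may stay impaired for long periods after malnutrition, which makes a rapid recovery of flow less obvious. Drift is a possibility the design cannot exclude, not a demonstrated fact.
- **That the paired t-test percentages describe the planned analysis.** The plan names ANOVA with Tukey's contrast, which gives lower figures. The inflation remains under both.
- **That the blinding statement should go.** It concerns the assessments of saliva and nutritional status. Masking analysts to nutritional status still serves the planned correlation with malnutrition.

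The cross-sectional label can fit the secondary objectives, which describe malnutrition and saliva. It does not fit the laser component.

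An article may leave detail to a fuller protocol. Here, however, the article itself states both the aim and the comparison, and the two do not match.

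**Conclusion.** The concern holds, confined to the mismatch between the aim and the planned comparison. As written, the plan can estimate how flow and IgA change over about 14 days in children given laser. It cannot attribute that change to laser.

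If the laser were inert, an assumed drift of 0.2 to 0.4 SD of within-child change would yield a significant increase in about 28% to 79% of trials by paired t-test, or about 17% to 67% by a Tukey contrast over three assumed time points. Without drift the rates are 2.5% and about 1%. The drift sizes, the number of time points and the equal SDs of change are assumptions. The conclusion depends on none of them, only on the absence of a concurrent comparison in the visible text.

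**What to change.** **Required, wording only:**

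1. In 2.1 and 2.3.1, describe the laser component as a single-arm before/after study. The cross-sectional label may stay for the descriptive objectives.
2. In the Background, restate the primary aim as estimating the change in salivary flow rate and IgA over 14 days in children given laser, and state that this change cannot be attributed to laser.
3. In 2.4, remove the allocation-sequence wording or explain what it does (for example, that it issues identifiers), since no arms are described.
4. Keep the masking of analysts to nutritional status.

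**Optional, only if the sponsor wants to keep the causal aim:** add a concurrent randomised comparison among the same 50 children, analysed between groups with adjustment for baseline. The cost is extra saliva collections and a detectable difference of about 0.81 SD (25 versus 25, before baseline adjustment) instead of 0.40 SD for the uncontrolled change. That trade-off is for the sponsor to weigh.
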